There are several different kinds of exogenous progesterone such as intramuscular, orally, vaginally, and trans-rectum [5]. The vaginal progesterone has been most widely used in ART because of its convenience and uterine first-pass effect. Vaginal P rapidly reaches the systemic circulation, and the steady state in the serum is achieved around 48–50 h such as Utrogestan 600 mg in a day, so its serum measurement on the day of ET seems reliable. Besides, a previous study showed that increasing doses of vaginal P do not proportionally increase serum concentrations [6]. In fact, the uptake, absorption, and metabolism of progesterone can vary among individualized patients [3]. If there is an optimal serum progesterone level, this problem might be solved by increasing the P dose from the very beginning or other optimal times, but has not yet to be demonstrated. The latest prospective study concluded that low serum progesterone on the day of embryo transfer was associated with a diminished ongoing pregnancy rate in oocyte donation cycles after artificial endometrial preparation [7]. We raised the question that if progesterone added on the day of ET can improve the outcome. So, it is necessary to explore this issue in the prospective controlled study.

According to this background, we design a prospective study to explore if serum P levels on the day of ET are related with clinical pregnancy and ongoing pregnancy rate, and additional progesterone intervention is helpful to improve the outcome.

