### Inclusion criteria

The following are the inclusion criteria:
HRT-FET cycles, including GnRHa-HRT-FET.Age < 41 years old.BMI < 30 kg/m^2^.TSH and PRL normal (0.27–4.0 mu/L for TSH and < 26 ng/mL for PRL)Endometrium thickness ≥ 8 mm on D0.Embryo transfer completed with at least 1 top-quality embryo (7–9 cell grade 1 or D5 beyond grade 3) within 2 embryos.Luteal phase support: transvaginal progesterone (Utrogestan) 600–800 mg/day with or without oral progesterone (dydrogesterone) 10 mg bid.Each patient is recruited only once.

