### Sample size calculation

A power analysis was performed according to the results from our own retrospective analysis, concluding a significant decrease in clinical pregnancy rate (CPR) when progesterone was < 7.24 μg/L (the first quartile) of 34.67% compared with ≥ 7.24 μg/L of 51.55% (*P* = 0.029).

The sample size was calculated in a two-sided test (80% statistical power, 95% confidence interval).

Low serum progesterone group: 1:1 intervention (A1) and control group (A2); high serum progesterone group: 1:1 to control group (B)

Group sample sizes are separated: 134 in group A1 and 134 in group A2 and 134 in group B. The test statistic used was the two-sided Fisher’s exact test. The significance level of the test was targeted at 0.05.

The formula is as follows:
$$ n=\frac{{\left({Z}_{1-\alpha }+{Z}_{1-\beta}\right)}^2\times \left({p}_1\left(1-{p}_1\right)+{p}_2\left(1-{p}_2\right)\right)}{{\left(\varepsilon -\delta \right)}^2} $$

After considering 5% of dropouts, 432 patients were recruited in total.

Age, BMI, endometrial thickness, serum E2, and number of transferred embryos were included in the analysis, regardless of their *P* values. Biochemical pregnancy is defined as serum HCG level ≥ 20 U/L. Clinical pregnancy is defined as observable gestation sac by transvaginal ultrasound. Ongoing pregnancy is defined as clinical pregnancy beyond gestational week 12.

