### Procedures

#### Study protocol (endometrial preparation)

All the included patients receive HRT for endometrial preparation. Treatment starts on day 2 or day 3 of menstruation with oral estradiol valerate administration (Progynova®, Bayer Guangzhou, China)—constant dose 4–8 mg/d or step-up increasing dose protocols, and the endometrium thickness will either be checked once during the first 5–7 days. The estradiol dose will be adjusted accordingly. After about 10–14 days of estrogens, a transvaginal ultrasound will be performed to measure the endometrial thickness and to confirm a triple layer pattern. Patients are considered ready for ET once endometrial thickness reaches 8 mm, and quiescent ovaries are detected by ultrasound, serum E2 > 150 pg/mL, and the serum P level < 2 ng/mL. Transvaginal P (Utrogestan® Besins, France) will be administered 3 or 5 days before embryo transfer at a dose of 200 mg tid or 400 mg bid Utrogestan vaginally. Transvaginal progesterone will be started 3 days before embryo transfer for patients who will have day 3 embryo transferred or 5 days before embryo transfer for those who will have day 5 embryo transferred. Serum progesterone will be tested on the morning of D3 (after 3 days of progesterone addition) after the first dose of progesterone, approximately 2 h beforehand. In case of pregnancy, HRT was maintained until gestational weeks 10. The estrogen would be gradually decreased with dosage after gestation at 8 weeks. The progesterone dosage would be not changed.

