#### Selecting patients

On the first day of progesterone supplementation (day 0), eligible patients are selected for this study. After checking all the inclusion and exclusion criteria, patients will be informed about the nature of the study, read the informed consent (IC) form, and decide if they wish to participate. After signing the IC form, a blood test of progesterone is performed on day 3. According to the serum progesterone level on day 3, if P is ≥ 7.24 ng/mL, continue with the transvaginal progesterone until the pregnancy test on days 14–16. If P < 7.24 ng/mL, according to the randomization numbers, the patient is randomized to either non-intervention control group or intervention group with intramuscular progesterone 40 mg until the pregnancy test on days 16–17. This protocol will continue until gestation week 8 and withdraw the intramuscular progesterone.

The included patient should test the serum progesterone level on D3 no matter which day the embryo transfer will be performed. According to the progesterone level, there are two groups:
Group A: serum progesterone < 7.24μg/L, followed by randomized:
A1: plus additional treatment (intramuscular progesterone 40 mg per day from D3)A2: without additional treatmentGroup B: serum progesterone ≥ 7.24μg/L, without additional treatment

Samples will be tested by the Beckman chemiluminescence method (Beckman DXI800, Roche, USA). The intra- and inter-assay variation coefficients for the P determinations were 6.11–11.19% and 7.51–9.57%, respectively, for *P* values between 1.26 and 22.61 ng/mL. The intra- and inter-assay variation coefficients for the E2 determinations were 2.4–10.5% and 2.4–9%, respectively, with a measurement range of 50–120 pg/mL.

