However, on the third day after the conversion of progesterone, it is found that the progesterone is lowered. What should be done next, cancel the transfer cycle, continue the transfer with progesterone as originally planned, or delay the transfer time are issues worthy of clinical research. Our study is based on the results of a single-center retrospective data analysis, combined with the progesterone results on the pregnancy test day and the clinical pregnancy outcome analysis. As the cutoff for optimal serum progesterone is inconsistent in various reports. It may be related to the characteristics of patients and differences in laboratory tests of progesterone. Our own retrospective analysis following quartiles are used as cutoff values to estimate the sample size and design a randomized controlled clinical study. The 3-day low cutoff progesterone patients were randomly divided into groups to receive intramuscular progesterone 40 mg, whether to improve the clinical outcome, hoping to provide a basis for clinical decision-making.

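### Background luteal regimen is neither a stratum nor a listed covariate, so the non-randomised low-versus-high progesterone comparison (A2 v B) may be confounded by regimen

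*Protocol article*

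**What the plan says.** Inclusion criteria, on permitted background treatment: "Luteal phase support: transvaginal progesterone (Utrogestan) 600–800 mg/day with or without oral progesterone (dydrogesterone) 10 mg bid". Study protocol (endometrial preparation) gives the two vaginal schedules: "at a dose of 200 mg tid or 400 mg bid Utrogestan vaginally". The same section times the D3 blood sample relative to a dose, "after the first dose of progesterone, approximately 2 h beforehand". The wording is unclear, but it reads most naturally as about two hours after that morning's dose.

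Selecting patients uses one threshold for everyone. On the low side: "If P < 7.24 ng/mL, according to the randomization numbers, the patient is randomized". On the high side: "if P is ≥ 7.24 ng/mL, continue with the transvaginal progesterone". The Discussion gives the source of the threshold: "Our own retrospective analysis following quartiles are used as cutoff values to estimate the sample size". The regimen mix of that retrospective cohort is not stated.

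Randomization and blinding stratifies by D3 or D5 transfer only. Sample size calculation lists covariates: "Age, BMI, endometrial thickness, serum E2, and number of transferred embryos were included in the analysis". Regimen is in neither place.

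The low-versus-high comparison is a stated aim. Background says the study is designed "to explore if serum P levels on the day of ET are related with clinical pregnancy and ongoing pregnancy rate". Expected repercussions adds that similar ongoing pregnancy rates in all three groups would mean that serum progesterone does not predict outcome.

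**The concern.** Groups A and B are formed by a measured level of the hormone that the women are already taking, and the amount taken varies. If women on one schedule are more likely to fall below 7.24, A and B will have different regimen mixes. Background and Discussion both say that vaginal progesterone reaches the uterus by a first-pass route and raises the concentration there. On the article's own account, then, the prescribed regimen could influence outcome by a path that does not run through serum level. Together these two links are what confounding of A2 v B requires.

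At stake is the serum-level objective and the three-group conclusion in Expected repercussions. Confounding could create a difference between A2 and B or hide one. The treatment question is not at stake. A1 and A2 are randomised after the cut-off has been applied, so their regimen mixes agree in expectation.

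**Working it through.** **The plan's own figure.** Sample size calculation uses clinical pregnancy rates of 34.67% (low) and 51.55% (high), two-sided 5% significance and 80% power. The pooled-variance formula for two proportions gives 134 per group, as stated. The planning difference is 51.55 − 34.67 = 16.88 points. It serves here only as a yardstick.

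**Inputs the article gives.** The daily vaginal doses are 3 × 200 = 600 mg and 2 × 400 = 800 mg, a ratio of 800/600 = 1.33. The cut-off is the first quartile of the retrospective data, so about 25% below it is a reasonable working value. Background says that serum concentration does not rise in proportion to vaginal dose, so 1.33 is taken as the upper end of the serum ratio.

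**Inputs that must be assumed.** Half of the women are on each vaginal schedule. Serum values are log-normal with log SD s of 0.4 or 0.5. Serum is r times higher on the larger daily dose, with r from 1.0 to 1.33. The direct effect of regimen on ongoing pregnancy, not through serum, is g = 10 points.

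**Formulas.** Let c be the log cut-off measured from the log-mean of the smaller-dose women. It solves 0.5·Φ(c/s) + 0.5·Φ((c − ln r)/s) = 0.25. Write L = Φ(c/s) for the chance that a smaller-dose woman falls below the cut-off.
- Smaller-dose share of A = 0.5·L/0.25 = 2L
- Smaller-dose share of B = 0.5·(1 − L)/0.75 = (1 − L)/1.5
- Shift in A2 v B = g × (share of A − share of B)

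A2 is a random half of A, so it has A's regimen mix in expectation.

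**One case in full.** With s = 0.4 and r = 1.33, ln r = 0.288 and c = −0.144. Then L = Φ(−0.36) = 0.360, and the chance for larger-dose women is Φ(−1.08) = 0.140. The smaller-dose share is 0.72 in A and 0.640/1.5 = 0.43 in B. The shift is 10 × (0.719 − 0.427) = 2.9 points.

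| r | s | P(low), smaller / larger dose | Smaller-dose share, A / B | Shift per 10 points |
|---|---|---|---|---|
| 1.0 | either | 0.250 / 0.250 | 50% / 50% | 0 |
| 1.1 | 0.4 | 0.288 / 0.212 | 58% / 47% | 1.0 |
| 1.1 | 0.5 | 0.280 / 0.220 | 56% / 48% | 0.8 |
| 1.2 | 0.4 | 0.321 / 0.179 | 64% / 45% | 1.9 |
| 1.2 | 0.5 | 0.307 / 0.193 | 61% / 46% | 1.5 |
| 1.33 | 0.4 | 0.360 / 0.140 | 72% / 43% | 2.9 |
| 1.33 | 0.5 | 0.339 / 0.161 | 68% / 44% | 2.4 |

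The shift scales with g: half these values for a 5-point direct effect, and nil if regimen has no effect on outcome apart from serum level.

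Dydrogesterone cannot be put through the same calculation. Nothing in the article says that it changes measured progesterone. It confounds A2 v B only if its use is associated with both serum level and outcome.

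**The case against.** The strongest reply is that no imbalance has been shown. The article reports no serum distribution, group membership or outcome by regimen. Background attributes serum variation to individual uptake and metabolism, says that serum does not rise in proportion to vaginal dose, and regards measurement on the transfer day as reliable. This stands as a limit on size. It weakens the link between dose and serum, but non-proportional does not mean absent.

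A second reply is that the covariate sentence is in the past tense, in a section that opens with the retrospective analysis, and may describe that analysis. The Statistical analysis section names no regression model, and covariates for a secondary comparison are often left to an analysis plan. The ambiguity is genuine, so the fix begins by settling it. If the list is meant for the trial, it is a stated list that omits the dose of the hormone defining the groups.

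A third reply is that the article speaks of relation and prediction, not cause. For pure prediction across usual-care regimens, an unadjusted comparison has its own meaning. That also stands, and it is why both analyses are asked for.

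A reader might go further and infer that the groups do differ by regimen, or that the objective is confounded as a matter of fact. The documents support only that they may. A reader might also use a serum ratio of 1.5, which gives shifts of 3.3 to 4.0 points. That exceeds daily-dose proportionality and sits badly with the Background statement.

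**Conclusion.** The point holds as a possible confounding of a secondary, non-randomised comparison. It is not a demonstrated error. One cut-off covers mixed regimens, regimen appears in neither the strata nor the listed covariates, and the article means to draw a conclusion that involves group B. Under the assumptions above, each 10-point direct regimen effect moves A2 v B by 0 to about 3 points, against a planning difference of 16.9 points. The shift is zero if regimen does not affect either classification at 7.24 or outcome. The true size cannot be estimated from the documents. The primary randomised contrast and the sample size are unaffected. The mixed regimens do mean that low progesterone may describe somewhat different women on different schedules, which matters when the result is applied.

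**What to change.** - In Sample size calculation, or better in Statistical analysis, state that the listed covariates apply to the trial's A2-versus-B analysis.
- Add vaginal schedule (200 mg tid or 400 mg bid) and dydrogesterone use (yes or no), both as recorded at D0. Add embryo stage (D3 or D5), which is already a randomisation stratum.
- Report the share of women below 7.24 by regimen, so that a reader can see whether A and B differ in mix.
- In Expected repercussions, base the statement on whether serum level predicts outcome on the adjusted as well as the unadjusted comparison.
- Clarify the sentence on when the D3 sample is taken relative to the dose.

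Regimen has to be known to check eligibility, so the main change is wording. The article does not say that it is entered in the case report form, and this should be confirmed. The statistical cost is a slightly wider interval for A2 v B. The sample size does not change, and no regimen or cut-off is proposed.

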### Exclusion criteria

The following are the exclusion criteria:
History of moderate and severe uterine adhesionPresence of hydrosapinx diameter > 2 cmEndometriosis at stages III–IVRecurrent implantation failure (> 3 times of embryo transfer cycle)PGT cycles

### Withdrawal criteria

Participation in the study is totally voluntary. The subjects can withdraw from the study at any time, and they will still receive standard medical care.

### Sample size calculation

A power analysis was performed according to the results from our own retrospective analysis, concluding a significant decrease in clinical pregnancy rate (CPR) when progesterone was < 7.24 μg/L (the first quartile) of 34.67% compared with ≥ 7.24 μg/L of 51.55% (*P* = 0.029).

The sample size was calculated in a two-sided test (80% statistical power, 95% confidence interval).

Low serum progesterone group: 1:1 intervention (A1) and control group (A2); high serum progesterone group: 1:1 to control group (B)

Group sample sizes are separated: 134 in group A1 and 134 in group A2 and 134 in group B. The test statistic used was the two-sided Fisher’s exact test. The significance level of the test was targeted at 0.05.

The formula is as follows:
$$ n=\frac{{\left({Z}_{1-\alpha }+{Z}_{1-\beta}\right)}^2\times \left({p}_1\left(1-{p}_1\right)+{p}_2\left(1-{p}_2\right)\right)}{{\left(\varepsilon -\delta \right)}^2} $$

After considering 5% of dropouts, 432 patients were recruited in total.

Age, BMI, endometrial thickness, serum E2, and number of transferred embryos were included in the analysis, regardless of their *P* values. Biochemical pregnancy is defined as serum HCG level ≥ 20 U/L. Clinical pregnancy is defined as observable gestation sac by transvaginal ultrasound. Ongoing pregnancy is defined as clinical pregnancy beyond gestational week 12.

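### The 134 per group is a chi-square sample size, but the protocol attaches its 80% power to a two-sided Fisher's exact test, which has about 77.5% power there

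*Protocol article*

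**What the plan says.** All the planning statements are in the protocol article, Sample size calculation.

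- **Rates.** Clinical pregnancy rates come from the centre's own retrospective analysis: "the first quartile) of 34.67% compared with" 51.55% at or above the progesterone cutoff.
- **Error rates.** "The sample size was calculated in a two-sided test (80% statistical power, 95% confidence interval"), and "The significance level of the test was targeted at 0.05".
- **Test.** "The test statistic used was the two-sided Fisher’s exact test".
- **Size.** "Group sample sizes are separated: 134 in group A1 and 134 in group A2 and 134 in group B".
- **Formula.** An unpooled normal-approximation formula is printed. It has Z(1−α) in the numerator and (ε − δ) squared in the denominator. Neither ε nor δ is defined.
- **Total.** "After considering 5% of dropouts, 432 patients were recruited in total". The Study sites section repeats 432.

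The Statistical analysis section assigns chi-square and Fisher's exact tests jointly to categorical variables. It does not say which of the two applies to ongoing pregnancy, the primary endpoint.

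**The concern.** Fisher's exact test is conservative at these sample sizes, so it needs more patients than the chi-square test for the same power. A size from a normal-approximation formula that is then credited to Fisher's test overstates the power. If the primary comparison (A1 against A2) is run with Fisher's test as the sample size section says, the trial falls short of its stated 80% even when every planning assumption is true.

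The printed formula adds to the doubt. Its quantile is the one-sided form, while the text says two-sided. It also carries a margin term that has no role in a plain two-sided comparison. A reader cannot tell from the section which calculation produced 134.

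**Working it through.** **Inputs** (all from Sample size calculation): p1 = 0.3467, p2 = 0.5155, difference 0.1688, two-sided α = 0.05, power 80%, equal groups. Quantiles: Z(0.975) = 1.960, Z(0.95) = 1.645, Z(0.80) = 0.842.

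**1. Reproducing 134.** The pooled two-sided formula, with p̄ = (0.3467 + 0.5155)/2 = 0.4311, is

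n = [1.960·√(2·p̄(1−p̄)) + 0.842·√(p1(1−p1) + p2(1−p2))]² / 0.1688²

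- 2·0.4311·0.5689 = 0.4905; its root times 1.960 is 1.3727.
- 0.2265 + 0.2498 = 0.4763; its root times 0.842 is 0.5808.
- n = (1.3727 + 0.5808)² / 0.02849 = 133.9, so **134**.

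The stated size therefore follows from the stated rates, α, power and sidedness.

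**2. Power of the named test.** For each pair of binomial counts at p1 and p2, I took the two-sided Fisher p-value and summed the probabilities of all pairs with p ≤ 0.05. The same was done for the Pearson chi-square test without continuity correction.

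| Per group | What it represents | Fisher power | Chi-square power |
|---|---|---|---|
| 134 | stated size | 77.5% | 81.0% |
| 137 | 432 less 5%, divided by three (136.8) | 77.3% | about 81% |
| 144 | 432/3 with no losses | 79.5% | above 80% |
| 145 | | 79.99% | above 80% |
| 146 | | 80.5% | above 80% |

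Fisher's power is not monotone in n, because the test is discrete; this is why 137 gives slightly less than 134. The continuity-corrected formula, which approximates Fisher, also gives 146. That is 146 − 134 = 12 more per group.

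**3. The printed formula.** Taking ε = 0.1688 and δ = 0 (assumptions, since neither is defined):

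- With Z(1−α/2), as a two-sided test requires: (1.960 + 0.842)² × 0.4763 / 0.02849 = 131.2, so 132.
- With Z(1−α) read literally at α = 0.05: (1.645 + 0.842)² × 0.4763 / 0.02849 = 103.3, so 104.

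Neither reading returns 134, because the printed variance is unpooled.

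**4. The dropout line.** 3 × 134 = 402 and 402/0.95 = 423.2, so 424. Rounding each group up gives 134/0.95 = 141.1, so 142 per group and 426 in total. The stated 432 implies 1 − 402/432 = 6.9% loss.

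**The case against.** The strongest reply is that 134 is correct for the stated inputs and that the Statistical analysis section already lists the chi-square test, under which 80% is met. On that view the reference to Fisher is a label slip with no consequence for patients. A gap of 2.5 points is also small beside the uncertainty in planning rates from a single retrospective analysis.

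Much of this stands. The size is not wrong for a chi-square test, and the shortfall is modest. But the analysis section names both tests and does not choose between them for the primary endpoint. The only sentence that ties one test to the power claim names Fisher. Under that test 80% is missed even if all 432 patients are evaluable (79.5% at 144 per group).

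Three stronger readings are tempting and are not supported:

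- *That the sample size does not reproduce from its own inputs.* It does, exactly, by the standard pooled two-sided formula.
- *That the correct size by the protocol's own formula is 104.* This needs Z(1−α) to be read as one-sided at 0.05, against a section that says two-sided, and a value for an undefined δ. With the two-sided quantile the formula gives 132, two below the stated figure. This is a notation fault; no patient number follows from it.
- *That 432 is an error in the recruitment target.* It exceeds the 5% figure by 6 to 8 patients (1.4% to 1.9%) in the safe direction. It equals 3 × 144, so rounding up is plausible, although the protocol does not say so.

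**Conclusion.** Wrong as written, and minor. The section attributes 80% power at 134 per group to a two-sided Fisher's exact test. That test has about 77.5% power at 134 and about 77.3% after the planned losses, and first exceeds 80% at 146 per group. The 134 belongs to the pooled two-sided z or chi-square test, which has about 81% exact power there.

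These figures take the protocol's planning rates as given, with equal groups, two-sided α = 0.05, and Fisher's p-value defined by summing all tables no more probable than the one observed. The 2.5-point shortfall applies only if Fisher's test is used for the primary endpoint, which the protocol leaves unsettled.

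**What to change.** 1. Name the Pearson chi-square test as both the planning test and the test for the primary endpoint, in Sample size calculation and in Statistical analysis. This keeps 134 per group with about 81% power and needs no extra patients. Alternatively, keep Fisher's exact test in both places and restate the power as about 77.5% at 134 per group.
2. Replace the printed formula with the pooled two-sided formula using Z(1−α/2), without the undefined δ, so that it returns 134.
3. Align the dropout line: either 5% with 424 (426 if rounded by group), or about 7% with 432.

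The first option costs only text. The Trial status section reports enrollment still ongoing at submission, so the primary test can be fixed before the final data are analysed.
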